### Data analysis

#### Quantitative analytic plan

Quantitative data will be analyzed using Stata. We propose two primary performance outcomes. The first is the difference between baseline and exit assessment in the percentage of eligible patients who receive screening for UAU (and drug risk when using Oregon’s SBIRT protocol), brief intervention, and MAUD. Because baseline levels may be strongly correlated with change, we also plan to conduct a sensitivity analysis to scale the change as a proportion of the initial gap between baseline and target. The second outcome is whether the clinic can report the Oregon CCO SBIRT metric to its regional CCO by the end of the study. These outcomes will serve as the dependent variable of a linear (percentage difference) or logistic (ability to report CCO measure) regression model.

To evaluate the impact of tailored implementation support on SBIRT, MAUD, and QI capacity (Aim 2), we will combine data on clinics’ previous collaborations with ORPRN, how clinics were referred to ANTECEDENT and the number and types of contacts in the recruitment and implementation phases. We will use logistic regression to determine which factors increase the probability of successful recruitment and project completion. In addition to the predictors above, we will account for the possibility that the level of implementation success depends on the specific practice facilitator or CCO. We anticipate that higher-intensity contact will be negatively associated with clinic enrollment but positively associated with study completion (defined as participation in exit assessment). We further hypothesize that implementation support will be most effective when clinics have a QI lead and clinic champion.

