### Clinic eligibility and recruitment

Any clinic in Oregon providing primary care to adult patients is eligible for the study. Prior work by our team identified approximately 750 primary care clinics in Oregon that meet eligibility criteria; we aim to engage approximately 20% of potentially eligible sites [35]. ANTECEDENT uses a rolling recruitment process to capitalize on changing capacity and interest in clinics, health systems, and CCOs over time. Clinic recruitment begins with engagement and outreach to regional CCOs and clinics with established ORPRN relationships. Prior research in Oregon suggests that larger and system-affiliated clinics are prioritized for support by the CCOs [36]. Thus, recruitment activities focus on reaching small- to medium-sized clinics (defined as clinics with fewer than 10 primary care providers) and independent clinics.

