#### Supplemental support

Prior work highlights dedicated staff’s value in supporting and implementing guidelines and toolkit resources into clinical workflows and practices [15, 44, 45]. Thus, we also seek to provide supplemental implementation support, coordinated by a trained practice facilitator, to interested clinics. Supplemental support may include practice facilitation, HIT support, peer-to-peer learning collaboratives, and expert consultation via academic detailing. Academic detailing is an interactive educational outreach to providers and staff to disseminate evidence-based information about prescribing practices and therapeutic decision-making to improve patient care [46]. HIT support includes generating data to inform changes to workflows and reporting for Oregon’s CCO SBIRT metric [27]. If the Oregon CCO metric cannot be generated or is not desired by the clinic, the practice facilitator will explore alternative measures, including the National Quality Forum 2152/ Centers for Medicare & Medicaid Services 431 or help develop a custom EHR query [47]. See Table 3 and S2 Appendix for additional detail on the supplemental support strategies.

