Supplemental implementation support plan	To lay out anticipated implementation support plan for each clinic.	Developed by practice facilitator	Within four weeks of clinic baseline assessment
Practice facilitator key informant interviews	To explore how individual facilitators tailor implementation support and the development of personal expertise.	Interviews with practice facilitators	Every six months
Periodic group reflections with practice facilitators	To explore how facilitators tailor implementation support, identify patterns in implementation across clinics, and track adaptations.	Facilitated debriefs with practice facilitators	Monthly
SBIRT and MAUD performance data collection	To identify the proportion of eligible patients receiving SBIRT and MAUD (outcome dependent variable) and ability to report the Oregon CCO metric to their regional Medicaid organization.	EHR or manual tracking	Baseline and exit assessment
Clinic key informant interviews	To understand how clinics experience implementation support and practice facilitator development over time; to understand tailoring of implementation support and facilitator skill development.	Interviews with clinic primary point of contact	Exit assessment

^a^ Baseline assessment activities occur within the first three months of project initiation

^b^ Exit assessment activities occur within the last three months of project support (months 13–15)

CCOs = Coordinated Care Organizations; SBIRT = Screening, brief intervention, and referral to treatment; MAUD = Medication-assisted treatment for alcohol use disorder; HIT = Health information technology; REDCap: Research Electronic Data Capture; EHR = Electronic health record

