#### Clinic baseline assessment

The baseline assessment includes five data points: The clinic intake form, needs assessment, workflow observations, HIT capacity assessment, and SBIRT and MAUD performance data collection (Table 4). The clinic intake form is a survey administered to collect details on clinic size, ownership, and electronic health record use. The clinic intake form includes an SBIRT and MAUD implementation checklist. This checklist will help determine a clinic’s capacity to capture and report data on intervention outcomes and inform tailored EHR support. The needs assessment addresses clinic practice culture, external context, and QI capacity. The observation of practice workflows will involve shadowing primary care clinicians and clinic staff to understand clinic culture and workflows related to SBIRT and MAUD. The HIT capacity assessment is used to gauge a clinic’s screening and tracking processes and ability to report the CCO SBIRT metric. In tandem, we will collect SBIRT and MAUD performance data using aggregate quantitative data from clinic EHRs or via manual chart audits. These final two data sources will inform the level of HIT support clinics receive to produce study outcomes data and CCO SBIRT quality metric reporting.

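### The second primary outcome is end-of-study reporting ability alone, so clinics already able to report at entry count as successes and prior capacity cannot be separated from gains during support

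*Protocol article*

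**What the plan says.** The Quantitative analytic plan names two primary performance outcomes and treats baseline differently in each.

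- **First outcome.** It is a change: "The first is the difference between baseline and exit assessment in the percentage of eligible patients who receive screening for UAU", and likewise for brief intervention and medication treatment. A safeguard follows: "Because baseline levels may be strongly correlated with change, we also plan to conduct a sensitivity analysis to scale the change as a proportion". The denominator of that proportion is the distance from baseline to target.
- **Second outcome.** It is a status at one time, "whether the clinic can report the Oregon CCO SBIRT metric to its regional CCO by the end of the study", analysed by logistic regression. No baseline component, restriction or companion analysis is stated.

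Reporting ability is nevertheless assessed at entry. Under Clinic baseline assessment, the HIT capacity assessment gauges "ability to report the CCO SBIRT metric", and that section says this assessment and the performance data inform the level of HIT support. In Table 4, the performance data row covers "ability to report the Oregon CCO metric to their regional Medicaid organization" and is timed at baseline and exit.

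Eligibility does not screen out clinics that can already report: "Any clinic in Oregon providing primary care to adult patients is eligible for the study". Study leadership and setting dates the metric from 2013. Aim 2 is to evaluate the impact of the support.

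The Supplemental support section also provides for another route: "If the Oregon CCO metric cannot be generated or is not desired by the clinic", the facilitator explores alternative measures.

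**The concern.** An outcome meant to show the impact of support should register what changed during support. Exit status gives the same score to a clinic that learned to report during the study and to one that could report on the day it enrolled.

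Two results are affected. The first is the headline exit proportion, whose floor is the share of clinics that were able at entry and stayed able. The second is the set of odds ratios. Baseline ability feeds into the amount of HIT support, so it is linked to the exposure, and it is likely to be a strong predictor of exit ability. It may also go with having a QI lead, a champion or routine performance data review, which Table 1 names as the conditions under which facilitation should work best. Clinics are not randomised, so nothing in the design removes this confounding.

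The authors recognised baseline dependence for the first outcome and stated no handling of it for the second.

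**Working it through.** **The article's own figure.** The only sample-size arithmetic is 150 × (1 − 0.20) = 120 clinics retained. It reproduces and is not in dispute. I use 120 below.

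**Inputs not in the article.** Let b be the share of clinics able to report at baseline, all assumed to stay able, and c the share of the remaining clinics that become able. The article gives neither, so every value of b and c here is an assumption.

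**1. Exit proportion.** The outcome as defined gives

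exit proportion = b + c(1 − b), and pre-existing share of successes = b / [b + c(1 − b)].

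| b | Unable at baseline, of 120 | Exit proportion, c = 0 | Exit proportion, c = 0.30 | Pre-existing share of successes, c = 0.30 |
|---|---|---|---|---|
| 0.20 | 96 | 20% | 0.20 + 0.30 × 0.80 = 44% | 0.20/0.44 = 45% |
| 0.40 | 72 | 40% | 0.40 + 0.30 × 0.60 = 58% | 0.40/0.58 = 69% |
| 0.60 | 48 | 60% | 0.60 + 0.30 × 0.40 = 72% | 0.60/0.72 = 83% |

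In the c = 0 column nothing was achieved, yet the outcome reads 20% to 60%. In the c = 0.30 column the conversion rate among clinics that could change is 30% in every row, while the reported proportion moves from 44% to 72%.

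**2. Odds ratio for support.** Take 120 clinics with b = 0.40, so 48 are able and 72 unable. Assume that 80% of unable and 20% of able clinics receive high support. Among unable clinics, assume 30% become able with high support and 10% without.

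- High support: 0.80 × 72 = 57.6 unable and 0.20 × 48 = 9.6 able. Successes are 9.6 + 0.30 × 57.6 = 26.88; failures are 67.2 − 26.88 = 40.32.
- Lower support: 14.4 unable and 38.4 able. Successes are 38.4 + 0.10 × 14.4 = 39.84; failures are 52.8 − 39.84 = 12.96.
- Odds ratio on exit status, unadjusted: (26.88/40.32) / (39.84/12.96) = 0.22.
- Odds ratio among clinics unable at baseline: (0.30/0.70) / (0.10/0.90) = 3.9.

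The sign reverses under these inputs. They were chosen to show the mechanism and do not estimate its size in this study.

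**The case against.** **Covariates may be settled elsewhere.** The article names the dependent variable and the model type but no covariate list for this model. An analysis plan that is not shown could adjust for baseline ability, and the absence of a list is no fault in an article. This stands as far as it goes. It does not reach the definition of the outcome, which the article does fix, or the unadjusted exit proportion that the definition yields.

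**Baseline capacity is used elsewhere.** The Mixed-methods convergence section classifies clinics by baseline capacity, support level and observed improvement. That is a partial answer: it serves the sorting of clinics, does not mention ability to report the CCO metric, and does not alter the logistic outcome.

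**The baseline share may be low.** Recruitment favours small and independent clinics, and the Exit assessment section expects some clinics to gain the capacity for baseline reporting through taking part. The 2013 date shows when the metric was introduced for CCOs, not how many clinics can produce it. This stands, and it is why no size can be claimed. Likewise, support that follows need is documented only for HIT support; supplemental support as a whole is optional.

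**Exit ability is a legitimate status measure,** and without a randomised comparison even a newly-able outcome would not isolate the effect of support. Both points are correct. The narrower claim is that exit status cannot distinguish gain from prior capacity.

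**Stronger readings that the text does not support.**
- A reader might infer that clinics not wanting the CCO metric are scored as failures. The wording is about whether a clinic can report, so a capable but unwilling clinic could be a success. The scoring is simply unstated.
- A reader might infer a group with no CCO to report to. No section identifies one.
- A reader might want every clinic without an exit assessment counted as not reporting. Missing exit data is a matter for the analysis plan, and that rule would misclassify dropouts who were able at entry. At most it is a sensitivity analysis.

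**Conclusion.** The point holds in a limited form. As defined, the second primary outcome counts prior ability as success. Neither its exit proportion nor an unadjusted odds ratio can be read as change during support, although Aim 2 asks about impact.

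The direction of the problem follows from the text: the exit proportion cannot fall below the share of clinics able at baseline that remain able. Its size cannot be derived. Over an assumed 20% to 60% already able and staying able, the floor is 20% to 60%. The reversal of the odds ratio is possible under the stated assumptions and is not shown to occur in this study.

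How clinics moved to an alternative measure are classified is a secondary ambiguity to clear up.

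**What to change.** 1. Define the second primary outcome as newly able to report the CCO SBIRT metric at exit, among clinics unable at baseline. If all clinics are kept, put baseline ability in the logistic model. If nearly all able clinics stay able, that term approaches separation, so restriction is the safer choice.
2. Take baseline ability from the HIT capacity assessment at entry, not from whether a baseline figure was eventually produced, since the article expects some clinics to acquire that capacity by taking part.
3. Show the baseline-by-exit 2x2 table for all assessed clinics, so that retained, gained and lost ability are each visible. The exit proportion can stay as a descriptive status measure.
4. State how a clinic is classified when it is steered to an alternative measure because the CCO metric is not desired.

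**Cost.** This is a change of wording; the data are already planned. The transition analysis has fewer clinics, 120 × (1 − b): 96, 72 or 48 for b of 20%, 40% or 60%. Its odds ratios will be less precise accordingly.

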### Implementation support

Implementation strategies are the methods or means by which target interventions are put into routine practice [38, 42]. Implementation strategies can be delivered as discrete strategies or bundles (e.g., a package of discrete concepts designed to address specific barriers and support implementation success) [38]. Facilitation is a multi-component implementation strategy [43]. As summarized in Table 3, ANTECEDENT implementation support is coordinated by a practice facilitator and uses a two-phase approach aligned with Proctor’s recommendations for reporting implementation strategies [42]. S1 Table and S2 Appendix provide additional detail about the timing and content of the implementation strategies, respectively.

**Table 3 pone.0269635.t003:** Implementation support strategies.

*Implementation Strategy*	*Definition*	*Dimension*				
		*The Actor(s)*	*The Action(s)*	*Action Targets*	*Temporality*	*Dose*
Foundational Support						
Baseline Assessment	Assessment of capacity, interest, and needs	Practice facilitators	Evaluate context, HIT capacity, and inform supplemental support	QI leads and care team	At baseline (recruitment)	One time: four to six hours
Implementation Toolkit	Implementation guide for SBIRT	SBIRT Oregon website	Provide asynchronous access to toolkit, resources, and training materials	Primary: QI leads Secondary: Practice facilitators	Ongoing	Number of visits and reported utilization
e-Screening SBIRT tool	Evidence-based tool for screening	Care team members	Provide a clinical decision support screener	Care team members	Ongoing	Number of documented screens
Exit Assessment	Assessment of capacity and impact	Practice facilitators	Evaluate context and produce data reports	QI leads and care team	After intervention	One time: three to five hours
Supplemental Support						
Practice facilitation	Process of interactive problem solving and support	Practice facilitators	Engage leadership; assess workflows; assist with changes; monitor and encourage progress	QI leads	Six months: two hours of (in person and/or virtual) practice facilitation per month	Visit length and intensity are tailored: up to 10 hours direct practice facilitator support

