#### Clinic contact logs

Following all clinic interactions, practice facilitators will record field notes in REDCap using structured forms containing open- and closed-ended prompts. Practice facilitators will use two types of structured note-reporting guides to record their interactions and clinic support. Brief communication logs will track short interactions with clinics (e.g., email outreach, scheduling), and in-depth intervention tracker forms will describe engagement, content, and the quality of scheduled facilitation meetings. The logs will produce evaluation data specified in the request for applications, such as the number and type of interactions and implementation strategies employed. The intervention tracker documents practice facilitator tailoring concerning clinic context and perceptions of clinic capacity for change. A qualitative analyst will regularly review the clinic contact logs for completeness.

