#### Exit assessment

All clinics will participate in an exit consultation, coordinated by the practice facilitator, in the final quarter of the intervention (months 13–15). The closing activities allow solidifying program maintenance and updating the clinic intake form (including the SBIRT and MAUD implementation checklist). During the exit assessment, we will also collect the second set of SBIRT and MAUD performance data to compare SBIRT and MAUD delivery rates to eligible patients at baseline and post-intervention per the specifications of the request for applications and external evaluation. We anticipate that some clinics will develop the capacity for baseline reporting via participation in the intervention. After completing these activities, the practice facilitator will connect the clinic point of contact to the qualitative team to complete the study exit interview. Additional information on the clinic intake form (baseline assessment) and exit interview (key informant interviews) are provided above and in Table 4.

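### Whole-phase contact counts depend on how long a clinic stayed in the phase, so their coefficients cannot show which factors raise completion or recruitment

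*Protocol article*

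**What the plan says.** For Aim 2, the Quantitative analytic plan combines each clinic's history with ORPRN, its referral route, and "the number and types of contacts in the recruitment and implementation phases". The purpose is explanatory: "We will use logistic regression to determine which factors increase the probability of successful recruitment and project completion".

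Completion is "defined as participation in exit assessment". The section Exit assessment places that event "in the final quarter of the intervention (months 13–15"). The expected directions are given in advance: "We anticipate that higher-intensity contact will be negatively associated with clinic enrollment but positively associated with study completion".

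The section Clinic contact logs says how contacts are recorded: "Following all clinic interactions, practice facilitators will record field notes in REDCap". Minor traffic is included: "Brief communication logs will track short interactions with clinics (e.g., email outreach, scheduling"). The exposure is thus described as a count by phase, and outreach and scheduling messages are among the logged items. For recruitment, the article says only that it is rolling; it does not say when outreach to a clinic ends.

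**The concern.** A count taken over a whole phase is contact rate multiplied by time in the phase, and the outcome helps to determine that time. A clinic that leaves in month 4 cannot collect the contacts of months 5 to 12; a completer can. The count therefore carries information about completion even if facilitators treat every clinic alike. This is the familiar immortal-time problem.

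Recruitment has a parallel, conditional on outreach practice. If outreach ends when a clinic accepts and continues when it does not answer, clinics that enroll will have fewer recruitment contacts.

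These artefacts can run in the directions the article predicts. A result that agreed with the prediction could be read as evidence that intensive contact keeps clinics in the study, and used to decide where facilitator time goes, when it may reflect only time in the phase.

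**Working it through.** **Figures in the article.** Enrollment: 750 × 0.20 = 150 clinics. Retention: 150 × (1 − 0.20) = 120. Both agree with the text and give 120 completers and 30 dropouts. The article gives no contact rate, test level or effect size for these models. Contact rates, dropout timing, chasing contacts, stop rules and a two-sided 0.05 level are therefore assumptions below.

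**Completion, expected counts.** Let every clinic have λ contacts per month, unrelated to dropout. Completers accrue for 12 months before the exit window; dropouts leave uniformly over months 0–12.

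- Completers: 12λ. Dropouts: 6λ.
- λ = 1: 12 against 6. λ = 2: 24 against 12.

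The whole gap is time at risk.

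**Completion, logistic regression on the total count.** No true effect, 150 clinics, 20% dropout, 500 runs per row:

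| Contact pattern | Chasing contacts per dropout | Median OR per contact | Significantly positive | Significantly negative |
|---|---|---|---|---|
| 1 per month | 0 | 1.57 | 100% | 0% |
| 2 per month | 0 | 1.39 | 100% | 0% |
| 1 per month, rate varying between clinics (gamma, variance 0.5) | 0 | 1.13 | 94% | 0% |
| As above, 40% of clinics at a quarter of the rate | 0 | 1.12 | 78% | 0% |
| Same | about 3 | 1.02 | 5% | 0% |
| Same | about 6 | 0.98 | 0% | 16% |
| 1 per month, no variation | about 6 | 1.00 | 6% | 4% |

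The means explain the pattern. With 40% low-contact clinics the average rate is 0.6 × 1 + 0.4 × 0.25 = 0.70 per month, so completers average 8.4 contacts and dropouts 4.2. Three chasing contacts bring dropouts to 7.2; six bring them to 10.2, above the completers. In the last row, 6 + 6 = 12 equals the completers' 12.

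**Shorter support.** The article's stated lengths differ: 12 months (Abstract), nine (Supplemental implementation support plan), six (practice facilitation, Table 3). Runs with 1.5 contacts per month and 40% low-contact clinics gave these rates of significantly positive results under the null:

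- contacts confined to months 3–9: 61–77% with no chasing, 0–0.3% with three chasing contacts per dropout;
- a nine-month period: 81–96% and 13–34%.

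Further null runs with 150 clinics and 20% dropout gave 83–100% with no chasing, 0–42% with three chasing contacts and 0% with six.

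**Completion with exposure separated from time.** With varying rates and no chasing:

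- contacts per month at risk: median OR 1.04, significant in 3% of runs each way;
- contacts in the first three months, among clinics still active then: median OR 1.00, 2% each way.

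In the further runs, a landmark three months into support gave 1–5% in total.

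**Enrollment, decision unrelated to contact.** 750 clinics, 20% enrolling, 200 runs. Enrollees accept after 1–3 contacts (mean 2).

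- Half of non-enrollees refuse after 1–3 contacts, half are contacted six times (mean 0.5 × 2 + 0.5 × 6 = 4): OR 0.53, significantly negative in 100%.
- All non-enrollees refuse after 1–3 contacts (mean 2): OR 1.01, 4% positive, 1% negative.
- As in the first case, but about three set-up contacts per enrollee are counted as recruitment (2 + 3 = 5 against 4): OR 1.27, significantly positive in 100%. Other set-up scenarios gave 2.19 and 2.59.

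**Enrollment, constant chance per contact.** Let each contact bring acceptance with chance a and refusal with chance r, up to K contacts. Then P(enroll) = a/(a+r) × [1 − (1−a−r)^K]. For a = r = 0.06 and K = 6: 0.5 × (1 − 0.88^6) = 0.268.

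| a | r | K | P(enroll) | Median OR per contact | Significantly negative |
|---|---|---|---|---|---|
| 0.05 | 0.02 | 6 | 0.252 | 0.41 | 100% |
| 0.06 | 0.06 | 6 | 0.268 | 0.60 | 100% |
| 0.06 | 0.12 | 6 | 0.232 | 0.73 | 100% |
| 0.06 | 0.24 | 6 | 0.176 | 0.85 | 85% |
| 0.10 | 0.40 | 10 | 0.200 | 1.00 | 4% |

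Here further contact can only add chances to enroll, yet the OR per contact is below 1 whenever many clinics are contacted up to the cap. It is 1.00 when refusals end nearly all contact. No fixed-window version was run for enrollment.

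**The case against.** Several objections have force.

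- **The artefact is not certain.** A reader might infer that both predicted signs will appear whatever contact does. The documents do not support that. Outreach and scheduling messages are logged, and a few of them per dropout can cancel or reverse the completion sign. The enrollment sign needs a stop rule that the article does not give. This stands. It also means that, with no contact effect, the coefficient depends on chasing and logging habits.
- **Support is optional.** Clinics with foundational support alone can complete with few contacts, which weakens the artefact. This stands, and the low-contact rows reflect it.
- **Intensity may be defined elsewhere.** A full analysis plan could turn it into a rate or a fixed-window measure. That is possible. But the article does more than leave a detail open: it names the number of contacts in the two phases as the predictor, and typed counts share the problem.
- **Exit-assessment contacts.** Table 3 gives this activity as "One time: three to five hours", and a reader might infer that those hours enter the predictor. Table 3 times it after the intervention, and nothing says it is counted. An explicit exclusion is prudent, but counting it is not an established error.
- **Implementation contacts as predictors of enrollment.** The sentence can be read that way. The natural pairing is recruitment contacts with enrollment and implementation contacts with completion.
- **Hyp 2a.** It concerns prior ORPRN relationship and CCO handoff. One might infer that contact counts distort those coefficients, but nothing here shows it.
- **Wording and place.** The prediction speaks of association and is not a Table 1 hypothesis. True, but the model's stated purpose is to find what increases the probability of each outcome.

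**Conclusion.** The point holds in conditional form. A whole-phase contact count can produce the predicted positive association with completion without any contact effect. With no chasing contacts, and depending on the assumed length of support, this happened in 61–100% of null runs. With about three chasing contacts per dropout the range was 0–42%, and with about six a significantly negative result occurred in up to 16%. For enrollment, the predicted negative association arises without a contact effect only if outreach ends at acceptance and enough non-responders are contacted further. It vanishes if refusals end contact equally early, and reverses if set-up contacts are counted.

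The coefficients therefore cannot show which factors increase the probability of recruitment or completion, whichever sign they take. The sizes rest on assumed contact rates, uniform dropout over 12 months and assumed outreach rules; only the 150 clinics, 20% attrition and roughly 20% of 750 enrolled come from the article. The two primary performance outcomes and their regressions are untouched. Severity: should fix.

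**What to change.** **Completion.** Replace the whole-phase count with one of these:

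- a discrete-time dropout model with monthly facilitation contacts, lagged so that exposure precedes the month at risk; or
- the contact count in a fixed window of the support period after the baseline assessment (for example the first three months of support), among clinics still active when the window closes.

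The first three project months are unsuitable as the window because they are the baseline assessment period and may hold little facilitation. In either version, exclude exit-assessment contacts and chasing or scheduling contacts.

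**Enrollment.** Use only exposures fixed before the decision: source and mode of first contact, or contacts in a fixed early window among clinics still undecided at its end. A discrete-time model by contact attempt is an alternative. State that implementation-phase contacts are not used.

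**Cost.** Only the analysis wording changes, since every interaction is already logged. Clinics lost before the window closes must be described separately, and some precision is lost.
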